### Ethics

The study is being conducted in accordance with the Helsinki Declaration. It was approved by the Ethics Committee of each recruitment sites: 1) Sherbrooke - Centre Hospitalier Universitaire de Sherbrooke and Centre de Santé et de Services Sociaux de l’Institut Universitaire de Gériatrie de Sherbrooke; 2) Montréal - Centre de Recherche Interdisciplinaire en Réadaptation de Montréal Métropolitain; 3) Longueuil - Centre de Santé et de Services Sociaux Champlain-Charles-Le Moyne; 4) Toronto - Sunnybrook Hospital. It has also been registered under http://www.clinicaltrials.gov (NCT01848080).

### Interventions

A personalized exercise program based on Tai Chi was developed by our team for previous studies aiming to improve balance in older individuals with diabetes [28] and in frail, older individuals with balance problems [29]. This program was also used during the pilot study. The exercise program consists of movements based on a combination of alignments and body-specific orientations, weight transfers and changes in direction inspired by Tai Chi [41]. The exercises do not require any physical interaction between the Tai Chi instructor and participants. Optimal treatment frequency for patients in the subacute and chronic phases following a stroke is twice a week, as suggested by a systematic review [42].

For both groups, the interventions will start immediately after discharge from hospital. The rehabilitation exercise sessions will be conducted by a physiotherapist trained in the practice of Tai Chi. The sessions will last 45 minutes and take place twice a week for eight weeks. The only difference between the groups will be the delivery mode of the intervention, that is telerehabilitation or home visits.

### Outcomes

All evaluations will be completed in the research centers/hospitals of the three sites and will last approximately three hours. The first evaluation will be conducted at baseline, prior to starting intervention (T_1_) to collect base measures on the participants’ condition. A second evaluation will be conducted just after the two-month intervention (T_2_) and the third evaluation will be four months (T_3_) following discharge from the hospital. All evaluations will be carried out by evaluators trained in the standard procedures for all measures, who are independent and blinded to the intervention. Specific directions will be provided to the evaluators and the participants to ensure that intervention allocation remains anonymous.

To measure balance and functional mobility, the Community Balance and Mobility Scale (CB&M) [43-45] will be used. This tool was developed for ambulatory individuals following a traumatic brain injury [43]. It has been validated in individuals following a stroke [44,46]. It assesses 19 tasks. The items are rated on a six-point scale (from 0 = unable to perform, to 5 = able to perform independently), for a maximum total score of 95 points. The CB&M has demonstrated good intra-rater, inter-rater and test-retest reliability (ICC = 0.98 for all three cases) and high internal consistency (Cronbach’s alpha = 0.96) [43]. It has good convergent validity with the Chedoke-McMaster Stroke Assessment [47] for leg and foot (r = 0.61 and 0.63, respectively) and for lower extremity strength (r = 0.67) [44]. Furthermore, the CB&M has been shown to be sensitive to change from baseline at follow-up in community-dwelling, ambulatory individuals post-stroke (SRM (standardized response mean) = 0.83) [44]. In addition, the Berg Balance Scale [42,48] will be used to evaluate balance in patients. The Four-Squares Test will also be used. This test consists of moving in different preset directions: forward, backward and to the sides. The time required to complete the sequence is recorded. An execution time greater than 15 seconds is predictive of falling. This test has high inter-rater (ICC = 0.99), intra-rater (ICC = 0.98) and test-retest (ICC = 0.98) reliability in community-dwelling older individuals aged 65 years and over [49]. Also, for predicting falls, this test has good specificity ranging from 88% to 100% and a positive predictive value of 86% [49].

The physical abilities capacities measured will be: 1) walking speed, 2) walking endurance, 3) lower extremity strength, and 6) lower extremity movement capacity. Each of these abilities plays an important role in achieving optimal functional mobility. Walking speed will be evaluated using the Timed Up and Go test (TUG) [50]. The test consists of standing up from a chair, walking a distance of three meters, turning around and returning to the chair to sit down again. The test is timed to measure walking speed in seconds over a distance of six meters. The TUG demonstrates good convergent construct validity with moderate to strong correlations with walking using the Tinetti test (r = 0.53) and walking speed (r = 0.66) in an elders population aged 65 years and over [51]. It has also been shown that walking speed is related to use of gait aids and fall frequency [52]. It is a measure sensitive to change [53]. Walking endurance will be estimated by the distance covered in meters during the Two-Minute Walk Test [53,54]. The inter-rater and intra-rater reliability of this test is high (ICC = 0.99) [50]. General lower extremity strength will be measured with the Sit to Stand test (STS) [55]. The time required to complete five successive ‘sit-to-stand’ repetitions will be recorded [55,56]. The test-retest reliability of the STS is high (ICC = 0.89) [57]. There is also a strong correlation of the STS with walking speed over five meters (r = -0.66) and lower extremity strength (r = 0.47) [58]. Lower extremity movement capacity and postural control will be evaluated using the Chedoke-McMaster Stroke Assessment [59]. The impairment inventory determines the presence and severity of physical deficits, and allows patients to be classified according to Brunnstrom’s seven stages of motor recovery. This tool has good intra- and inter-rater reliability (ICC = 0.98 and 0.97, respectively) and good construct validity (r > 0.60 with different aspects of the Fugl Meyer test) [47].

Two main aspects of psychological capacities measured will be 1) fear of falling, and 2) self-efficacy. The simplified version of the Activities-specific Balance Confidence (ABC) scale [60] questionnaire (ABC-S) will measure fear of falling. This questionnaire includes 15 questions rated on a four-point Likert scale and evaluates an individual’s balance confidence during a series of daily activities [60,61]. The ABC-S has strong internal consistency (Cronbach’s alpha = 0.86) good convergent validity with significant associations with balance and occurrence of falls [60]. Self-efficacy when faced with difficult life situations will be evaluated using the Generalized Self-Efficacy Scale (GSES) [60]. This questionnaire is a ten-item scale that uses a four-point Likert scale (from 1 = not true at all, to 4 = completely true) to assess whether an individual believes that their actions are responsible for their successful outcomes. This scale has been shown to have excellent internal consistency (Cronbach’s alpha = 0.86) [62].

Quality of life will be measured using the Reintegration to Normal Living Index (RNLI) [63]. This tool consists of 11 items ranked on a three-point Likert scale. The total score ranges from 0 to 22, with higher scores depicting lower quality of life. The psychometric properties range from very good to excellent with good internal consistency (Cronbach’s alpha = 0.90) and good test-retest reliability (r = 0.83) [63]. The construct validity of this tool has been examined in a post-stroke population and shows excellent correlations with the Frenchay Activities Index (r = 0.69) and the Short Form 36 Health Survey (r = 0.74) [64].

Participant satisfaction with the intervention received will be evaluated using the Health Care Satisfaction Questionnaire, a questionnaire developed and validated in French [65]. The satisfaction construct is determined by three distinct factors which include satisfaction with: 1) the therapist relationship, 2) the services provided, and 3) the organization of services. This tool includes 26 questions, scored on a four-point Likert scale. The total score is calculated based on average satisfaction for the three factors, with higher scores indicating higher levels of satisfaction. Test-retest reliability is documented by an ICC of 0.72 and internal consistency by a Cronbach’s alpha of 0.93 for the entire scale [65].

A modified version of the ‘Cost analysis of telemedicine’ table from the University of Minnesota [66] will help tabulate the costs associated with the teletreatments. These costs will be calculated to establish a cost differential (that is, cost-effectiveness) between the two different types of intervention. The method for collecting this data has already been tested in a previous study [67]. The variables related to the total cost include those associated with the actual intervention (for example, direct and indirect time for the intervention, professionals’ travel time to the participants’ homes, telerehabilitation equipment, and Internet service including installation and set-up).

The typical sociodemographic (for example, age, sex, marital status, living environment, education, primary occupation) and clinical characteristics (for example, diagnosis, gait aid, medications, self-rated health, co-morbidities) will be collected using an in-house questionnaire, with the exception of comorbidities for which the Functional Comorbidity Index will be used [68].

The level of impairment post-stroke will be measured by the National Institute of Health Stroke Score (NIHSS) [69,70]. This questionnaire, administered by a healthcare professional, includes 15 items to evaluate patients in the acute post-stroke phase. It demonstrates good internal consistency (Cronbach’s alpha > 0.5) [71], good inter-rater (ICC = 0.69) and test-retest (ICC = 0.66 to 0.77) reliability in a post-stroke population [69] and good convergent validity (r = 0.74 with lesion volume seven days post-stroke) [70]. The level of cognitive impairment will be measured using the Montreal Cognitive Assessment (MoCA) [72]. This test evaluates attention, concentration, executive functions, memory, language, visioconstructive capacities, abstraction capacities, calculation and orientation. The maximum score of 30 corresponds to no cognitive problems. The internal consistency of this test is good (Cronbach’s alpha = 0.83) and test-retest reliability is excellent (ICC = 0.92) [73]. The correlation between the MoCA and Mini-Mental State Examination scores has been shown to be excellent (r = 0.87) [73]. Noteworthy is the fact that this test will be completed during the participant recruitment phase.

### Statistical methods

We expect to recruit 240 participants, that is, 120 per group. Allowing for a drop-out rate of 10%, this sample size will provide a power of 80% to demonstrate the non-inferiority of Tai Chi provided by telerehabilitation compared to Tai Chi provided in person at home, with a two-group one-sided test at the 2.5% level (nQuery Advisor 7.0; Statistical Solutions, Boston, MA). For this calculation, the non-inferiority limit was set at four points on the CB&M scale and the standard deviation of the gain was estimated to be 10.4, based on findings from Knorr [44], since SRM = Mean_GAIN_/s_GAIN_ implies that:

$$S_{\mathrm{GAIN}}={\mathrm{Mean}}_{\mathrm{GAIN}}/\mathrm{SRM}=\left(51.3-42.7\right)/0.83$$

First, we will describe the characteristics of each group pre-intervention using averages and standard deviations (continuous variables) or percentages (categorical variables). The groups will then be compared using a *t*-test or chi-squared test. If the groups differ on certain characteristics pre-intervention despite randomization, subsequent analyses will account for these differences.

Primary analysis will aim to test the non-inferiority of Tai Chi provided via telerehabilitation compared to Tai Chi provided in person at home as evaluated by score gains on the CB&M questionnaire from T1 to T2. Delivery by telerehabilitation will be regarded as non-inferior to in person home delivery if the upper limit of the unilateral confidence interval around the difference in gains between the two groups is less than 4. This non-inferiority limit was set below the CB&M’s minimal clinically significant difference of five points. It is recommended to choose a non-inferiority limit less than the difference judged to be clinically significant [74,75].

The same analytical strategy will be used to evaluate and compare the effectiveness of the interventions on secondary variables and to compare maintenance over time (that is, the confidence interval around the difference between the two groups from T1 to T3) across all variables. A more conservative level of significance will be used to account for the numerous tests.

All analyses will first be performed according to the treatment received (per protocol = PP) and according to the assigned group (intention to treat = ITT), requiring that non-inferiority be shown in both cases since ITT analyses increase the chance of declaring non-inferiority if the two delivery modes produce a similar pattern of withdrawal, while PP analyses bias towards the null in presence of a different pattern of withdrawal [74]. For the ITT analysis, the effects of withdrawal or low levels of compliance will be explored with sensitivity analyses, where the missing data will be replaced with extreme values (that is, no change following treatment - the most favorable change noted in the study). Any non-robustness of results revealed by the comparison of strategies will be noted and the caveats will be mentioned in the discussion of results. All analyses will be conducted at the end of the study since the proposed treatments are of short duration and involve minimal risk to the participants.

The economic analysis will be a type of cost-minimization study [76]. Assuming that the effectiveness will be the same in the dependent variable (CB&M), the cost will be determined for the two groups and the cost differential will be established.

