Participants will be recruited during the hospitalization period by the team of treating nurses, physiotherapists and neurologists at each of the three sites (Sherbrooke, Montreal and Toronto). When the team decides that a patient will not require a referral to an IFRU and will return home (inclusion criteria 1 and 2), they will verify inclusion criteria 3 and 4 and exclusion criteria 1 to 5 from the medical chart. If patients are eligible based on these criteria, the hospital team will ask if they agree to be contacted by a research associate. If they agree, a research associate will visit them in hospital to inform them of the project and ask them to participate. The research associate will verify inclusion criteria 5 and 6. If a patient meets all the criteria and is interested in participating in the study, they will be asked to sign the consent form previously approved by the ethics committee at each recruitment site.

Once included, participants will be randomly assigned to either the telerehabilitation group or the home visits group by the coordinator of each recruitment site. This randomization will be performed using block randomization of sizes 2 and 4 done by a computer. Block size will not be known by the evaluators. This randomization will be performed following stratification based on the Rankin score (2 or 3), a variable that is likely to influence recovery prognosis. A system of numbered, sealed envelopes will be put in place.

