Telehealth, which includes telerehabilitation, is seen as a method to provide care to the population. Considering that the criteria for quality of care remain the same regardless of whether the care is provided by telehealth or other means, the evaluation framework of the proposed research is based on the theoretical construct of quality of care. Without formal definition [77], quality of care encompasses two components: 1) the viewpoint of the patient who considers the notions of accessibility and effectiveness as essential [78]; and 2) the viewpoint of the professional for whom the patient-doctor relationship [79], efficiency and reliability are of key importance. Several conceptual models for evaluating quality of care in the literature include the Donabedian [80], Total Quality Management [81], Quality-Caring [82], ORYX [80], HEDIS [83] and CONQUEST [80] models. In this research project, the conceptual evaluation model used will be the Donabedian model [84]. Given the objectives of this project, the study aims to answer specific questions related to the effectiveness of using telerehabilitation to improve quality of care for older individuals. This model defines quality of care as a combination of three elements: structure, process and outcome. The notions of ‘quality’ and ‘performance’ are directly related to the organizational structure of the healthcare system and its management processes. The term ‘outcome’ corresponds to the quality of care provided to patients, the performance of the healthcare system in offering care and the associated costs. Given the nature of this research, emphasis will be placed on the evaluation of telerehabilitation outcomes.

Concerning internal validity, we will control for potential selection bias by assigning participants to either the telerehabilitation or the control (home visits) group by randomization and by comparing participants’ characteristics in each group before the intervention. If the groups have different characteristics pre-intervention despite randomization, subsequent analysis will account for these differences. Information bias will be controlled by using standardized measures and by calibrating all the assessors for each assessment.

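### Covariates for the primary analysis are to be chosen by testing randomised groups for baseline differences, which selects on chance imbalance instead of prognostic value

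*Protocol article*

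**What the plan says.** In the protocol article, Statistical methods, baseline characteristics are first summarised by group. Then: "The groups will then be compared using a *t*-test or chi-squared test". The next sentence sets the consequence: "If the groups differ on certain characteristics pre-intervention despite randomization, subsequent analyses will account for these differences". The paragraph after it describes the primary analysis, non-inferiority "as evaluated by score gains on the CB&M questionnaire from T1 to T2", and names no covariates.

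The Discussion repeats the rule as part of the control of selection bias: "If the groups have different characteristics pre-intervention despite randomization, subsequent analysis will account for these differences".

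The Participants section describes block randomisation, with block sizes 2 and 4, after "stratification based on the Rankin score (2 or 3), a variable that is likely to influence recovery prognosis". Nothing says that this factor enters the analysis. The article gives no threshold for calling the groups different, no list of candidate covariates and no form of adjustment. All analyses are to be run at the end of the study.

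**The concern.** In a properly randomised trial, the null hypothesis of each baseline test is true by construction. A significant result shows only that a chance imbalance happened to be large. It says nothing about whether the variable predicts the gain in CB&M. The rule can therefore bring in an irrelevant variable and leave out a strong predictor.

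The Rankin score shows this most clearly. The protocol calls it prognostic and stratifies on it in small blocks, so its distribution will be nearly equal in the two arms and a baseline test will almost never flag it. In practice the rule excludes the one predictor that the protocol names.

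This is not a detail left to a later analysis plan. The article states how covariates will be chosen, and an analysis plan with fixed covariates would have to override it. What is at stake is whether the model behind the primary conclusion is known in advance, and whether precision available from data already collected is used.

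**Working it through.** **Inputs from the protocol article.** Margin 4 points; SD of the gain 10.4; one-sided 2.5%; power 80%; dropout 10%; 120 per group (Statistical methods). Baseline items (Outcomes): six sociodemographic examples ("age, sex, marital status, living environment, education, primary occupation"), five clinical examples ("diagnosis, gait aid, medications, self-rated health, co-morbidities"), plus NIHSS and MoCA, which makes 13. A further ten outcomes could be scored at T1: CB&M, Berg, Four-Squares, TUG, Two-Minute Walk, Sit to Stand, Chedoke-McMaster, ABC-S, GSES and RNLI. That makes 23. The article does not say which of these will be tested.

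**1. The plan's own sample size.** SD = (51.3 − 42.7)/0.83 = 10.36, rounded to 10.4. The normal approximation gives n = 2 × 10.4² × (1.96 + 0.8416)²/4² = 106.1, so 107 per arm, and 107/0.9 = 118.9, so 119 per arm (238 in total). With the t distribution, 108 per arm gives 80.3% power, and 108/0.9 = 120 per arm, or 240. The stated figure reproduces, for an unadjusted two-group comparison.

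**2. Chance that the rule changes the model.** Assume k independent tests at 5% (neither is stated in the article). Then P(at least one flagged) = 1 − 0.95^k.

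| k | P(at least one flagged) |
|---|---|
| 5 | 22.6% |
| 10 | 40.1% |
| 13 | 48.7% |
| 20 | 64.2% |

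Several of the T1 outcomes measure related balance and mobility abilities. Positive correlation lowers these figures.

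**3. What the rule does to the primary test.** Simulation with 12,000 trials per scenario, 108 per arm, SD of gain 10.4, and 10 independent baseline variables. The rule adjusts for any variable with p < 0.05; the pre-specified model adjusts for the prognostic ones only. The correlations with gain are assumptions, since the article gives none.

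| Assumed correlations with gain | Power, unadjusted | Power, rule | Power, pre-specified | Type I error under the rule (true difference at the margin) |
|---|---|---|---|---|
| 0.4 | 79.8% | 80.2% | 86.4% | 0.023 |
| 0.4, 0.3 | 80.5% | 81.0% | 89.6% | 0.024 |
| 0.5, 0.3, 0.3 | 80.0% | 81.2% | 95.7% | 0.022 |

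The rule changed the model in about 40% of trials. It reversed the conclusion relative to the unadjusted analysis in about 3% to 4% of trials at a true difference of zero, and in about 1% at the margin.

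**4. Check of the first row by formula.** Adjusting for a covariate correlated 0.4 with gain reduces the SD to 10.4 × √(1 − 0.16) = 9.53. The standard error is 9.53 × √(2/108) = 1.30, so 4/1.297 − 1.96 = 1.12 and power is about 87%. This agrees with the simulation.

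**The case against.** The strongest defence is that the rule does little measurable harm. It keeps the planned 80% power, and the power it forgoes is relative to a model that was never planned, at assumed correlations. Stratification already balances Rankin, and a gain score deals with part of any baseline CB&M imbalance. The article also states no p-value criterion. That the tests decide whether groups differ is inferred from the two sentences standing next to each other. All of this stands, and it limits the size of the point. It does not justify the rule, because stratification and gain scores do not tell the analyst which covariates to use.

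A reader might infer more than the text supports:

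- **That the false-positive rate rises.** The simulation shows 0.022 to 0.024 under the rule, against a nominal 0.025.
- **That the estimand changes.** The target is a difference in mean gain. Linear adjustment for baseline variables in a randomised comparison targets the same quantity and mainly affects its precision.
- **That an imbalance just short of significance biases the result.** At 108 per arm that imbalance is 1.96 × √(2/108) = 0.27 SD. At a correlation of 0.4 it moves the difference by 0.27 × 0.4 × 10.4 = 1.1 points. But this is close to the worst case, it can go either way, and it is already covered by the unadjusted standard error of 10.4 × √(2/108) = 1.42. It is sampling error.
- **That the ITT and PP analyses will use different models.** The article describes one baseline comparison and does not say that it is repeated in each analysis set.

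**Conclusion.** The point holds as a badly fixed analysis rule that should be changed. As written, whether the primary analysis is adjusted, and for what, depends on chance imbalance. Under independent 5% tests that means a changed model about 49% of the time with 13 variables and 64% with 20, and less often with correlated variables. Adjustment lands on variables without regard to prognosis and practically never on Rankin.

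The demonstrated cost is lost precision: about 80% power against about 86% with one covariate correlated 0.4 with gain, and a wider gap if baseline predicts more. A second cost is not captured by the simulation. With no threshold, candidate list or form of adjustment stated, the model can be chosen after results are seen. The documents do not support a claim of invalid type I error or of a biased estimate when the rule is applied mechanically.

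**What to change.** - Delete the baseline tests and the conditional-adjustment sentence in Statistical methods, and the matching sentence in the Discussion. Present baseline data descriptively by arm.
- Pre-specify the primary model for the T1 to T2 gain with baseline CB&M and Rankin stratum as covariates. For secondary outcomes, use the baseline value of that outcome, where one exists, with Rankin stratum.
- Site may be added because allocation is carried out by the coordinator at each site. This is optional, since the Participants section names only Rankin as a stratification factor.
- List in advance any adjustment for other variables, such as age or NIHSS, and label it a sensitivity analysis.
- State that the ITT and PP analyses use the same covariates.

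The change is one of wording and removes an analysis step. Baseline CB&M and Rankin score are already collected, and the sample size of 240 need not increase.

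### The primary CB&M comparison has no pre-specified adjustment for baseline CB&M or the Rankin stratum; covariates enter only if baseline tests find a difference, which gives up precision

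*Protocol article*

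**What the plan says.** **Primary analysis (Protocol article, Statistical methods).** Non-inferiority is judged "as evaluated by score gains on the CB&M questionnaire from T1 to T2". It is declared if the upper limit of a one-sided confidence interval for the between-group difference in gains is below 4. No covariate is named for this comparison.

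**Sample size (same section).** "We expect to recruit 240 participants, that is, 120 per group". The calculation is made "with a two-group one-sided test at the 2.5% level", and "the standard deviation of the gain was estimated to be 10.4". It therefore rests on the SD of the raw, unadjusted gain.

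**Randomisation (Participants).** Allocation follows "stratification based on the Rankin score (2 or 3), a variable that is likely to influence recovery prognosis".

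**Covariate rule (Statistical methods, repeated in the Discussion).** The groups are compared at baseline by t-test or chi-squared test. Where they differ on some characteristic, later analyses will take that into account. No significance level or list of characteristics is given.

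**The concern.** The protocol collects CB&M at T1 and stratifies on a factor that it considers prognostic, yet its stated primary comparison gives neither a fixed place as a covariate.

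Subtracting baseline fixes its slope at 1. Estimating the slope is at least as precise in large samples, and more precise whenever baseline is related to gain. Leaving a prognostic stratification factor out of the analysis makes the standard error too large, because the balance that stratification imposes is not credited.

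The covariate rule does not repair this, for four reasons:

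- Stratified blocks of 2 and 4 keep Rankin nearly balanced, so a test is unlikely to flag the one factor named as prognostic.
- A test on baseline CB&M misses moderate imbalance, and the remainder passes into the gain difference through regression to the mean.
- Adjustment improves precision whether or not the groups differ, and the rule forgoes this when they look balanced.
- The primary model depends on results seen after randomisation.

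At stake is the chance of failing to show non-inferiority that is true. The sample was sized to its target with almost no reserve, and non-inferiority must be shown in both the ITT and the per-protocol analysis.

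**Working it through.** **Inputs from Statistical methods:** one-sided alpha 0.025, power 80%, margin 4, SD of gain 10.4, 120 per group, 10% drop-out. **Assumed, because the document gives neither:** the T1-T2 correlation r of CB&M (0.6 to 0.9), and equal variances at T1 and T2.

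**1. The plan's own figure.**
- SD of gain = (51.3 − 42.7)/0.83 = 10.36, which the article rounds to 10.4.
- n = 2 × (1.960 + 0.842)² × 10.4²/4² = 106.1, so 107 per group. Dividing by 0.90 gives 119, against 120 stated. The figure reproduces.
- Evaluable per arm: 120 × 0.90 = 108. Standard error = 10.4 × √(2/108) = 1.415.
- Half-width = 1.971 × 1.415 = 2.79 points. Power for a true difference of zero (noncentral t) = 80.3%.

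**2. Adjusting for baseline CB&M.** With equal variances, Var(adjusted)/Var(gain) = (1 + r)/2. The SD becomes 10.4 × √((1 + r)/2), still with 108 per arm.

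| r (assumed) | Variance ratio | SD | Half-width | Power |
|---|---|---|---|---|
| no adjustment | 1.00 | 10.40 | 2.79 | 80.3% |
| 0.9 | 0.95 | 10.14 | 2.72 | 82.3% |
| 0.8 | 0.90 | 9.87 | 2.65 | 84.3% |
| 0.7 | 0.85 | 9.59 | 2.57 | 86.3% |
| 0.6 | 0.80 | 9.30 | 2.50 | 88.2% |

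The variance saving is equivalent to 1/0.95 − 1 = 5% up to 1/0.80 − 1 = 25% more participants.

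**3. When the gain shrinks.** The saving depends on the correlation between baseline and gain. It tends to zero as r approaches 1 under equal variances, and is nil if baseline is unrelated to gain, which can happen when T2 varies more than T1.

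**4. What a baseline test lets through.** Equal variances imply a CB&M SD of 10.4/√(2(1 − r)): 11.6 at r = 0.6 and 23.3 at r = 0.9. Assume a two-sided 5% test with 120 per arm. A baseline difference passes unflagged up to about 1.97 × SD × √(2/120), and a fraction (1 − r) of it appears in the gain difference.
- r = 0.6: up to 1.97 × 11.6 × 0.129 = 2.95 points unflagged, shifting the gain difference by up to 0.4 × 2.95 = 1.2 points.
- r = 0.9: up to 1.97 × 23.3 × 0.129 = 5.9 points unflagged, shifting it by up to 0.1 × 5.9 = 0.6 points.

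Such shifts go in either direction and average to zero over randomisations. They are part of the variance in step 2, not an added bias.

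**5. Rankin.** The document gives no effect of Rankin on CB&M gain. For illustration only, if it explained 5% of the gain variance, the variance ratio would be 0.95 and power would rise to about 82.3%. Its contribution beyond baseline CB&M could be negligible.

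**The case against.** The strongest reply is that nothing here is wrong. Randomisation makes the comparison of gains unbiased. Omitting a stratification factor makes the interval conservative, so the error that matters most in a non-inferiority trial, a false claim, is not inflated. The sample size uses the same raw-gain SD as the analysis and reaches its target. All of this stands.

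A reader might infer that baseline CB&M is ignored, or that any chance imbalance goes straight into the result. The document does not support either. A gain already subtracts baseline, and the covariate rule provides adjustment when a difference is detected. Nor does the document support reading the trial as underpowered: 107 per group are needed and 108 are expected.

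It can also be said that the text names no test for the primary analysis, that a linear model of the gain would yield a difference in gains too, and that covariate lists are often left to an analysis plan, which is not shown here. This has some force, since such a plan may name the covariates. However, the article does more than leave the list open. It states how covariates will be chosen, by baseline tests, and that stated rule is the weak one.

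Finally, the size of the benefit rests on a correlation and a variance assumption from outside the document. That is correct, so it is given as a range with its limits.

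**Conclusion.** The point holds as one of lost efficiency and of a primary model not fixed in advance. It is not a point about bias, type I error or inadequate sample size.

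Under equal T1 and T2 variances and r between 0.9 and 0.6, pre-specified adjustment for baseline CB&M is worth 2 to 8 percentage points of power and narrows the interval by about 2.5% to 11%. The benefit is smaller if r is nearer 1, nil if baseline is unrelated to gain, and not quantifiable for Rankin from this document. The change is worth making because it uses data already collected and adds a reserve to a design with almost none, not because the present plan fails.

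**What to change.** Replace the baseline-test rule for the primary analysis with a pre-specified linear model of CB&M at T2 (or of the gain) on arm, T1 CB&M and Rankin stratum (2 or 3). Site may be added. Take the adjusted home-minus-telerehabilitation difference and compare its one-sided 97.5% upper limit with the unchanged 4-point margin. Use the same model for ITT and per-protocol, and for T3. Baseline tables can stay as description, without deciding the covariates.

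The cost is a sentence or two in the analysis plan, fixed before outcome data are examined. No new data are needed, and the margin and sample size do not change.
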